**Additional measures**				
Anthropometry	Height, weight, body mass index and waist circumference	×	×	×
Physical activity	Community Healthy Activities Model Program for Seniors questionnaire	×	×	×
Diet	Anti-Cancer Council Food Frequency questionnaire	×		×
	24-hour food recollection	×	×	×
Adverse events	Monthly phone calls	Collected from monthly calls		
Programme adherence	Calculated from monthly calendars collected every 8 weeks	Collected every 8 weeks		
Supplement compliance	Calculated from supplement and sachets returned at 3 and 6 months		×	×

HOMA, homeostasis model assessment.

#### Primary outcome measures

The primary outcome measures will be changes in glycated haemoglobin levels (HbA_1c_) and homeostasis model assessment 2 (HOMA-2) of insulin resistance and β-cell function based on model-derived estimates using the validated HOMA-2-calculator [37], version 2.2.3, from fasting glucose and insulin measured at least three days after the last PRT session. All data will be checked prior to importing into the calculator, and extreme values of fasting plasma glucose ≤3 or ≥25 mmol/l or serum insulin <20 or >300 pmol/l will be excluded, as this is the validity range of the HOMA-2 calculation, based on specific insulin measures. More specific details of the blood collection and methodology for assessing these measures are provided later.

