**Methods/Design:**

Using a two-arm randomized controlled trial, this 6-month study builds upon the community-based progressive resistance training (PRT) programme *Lift for Life®* to evaluate whether ingestion of a whey-protein drink combined with vitamin D supplementation can enhance the effects of PRT on glycaemic control, body composition and cardiometabolic health in older adults with type 2 diabetes. Approximately 200 adults aged 50 to 75 years with type 2 diabetes, treated with either diet alone or oral hypoglycaemic agents (not insulin), will be recruited. All participants will be asked to participate in a structured, supervised PRT programme based on the *Lift for Life®* programme structure, and randomly allocated to receive a whey-protein drink (20 g daily of whey-protein plus 20 g after each PRT session) plus vitamin D supplements (2000 IU/day), or no additional powder and supplements. The primary outcome measures to be collected at baseline, 3 and 6 months will be glycated haemoglobin (HbA_1c_) and insulin sensitivity (homeostatic model assessment). Secondary outcomes will include changes in: muscle mass, size and intramuscular fat; fat mass; muscle strength and function; blood pressure; levels of lipids, adipokines and inflammatory markers, serum insulin-like growth factor-1 and 25-hydroxyvitamin D; renal function; diabetes medication; health-related quality of life, and cognitive function.

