### Statistical analysis

The primary statistical analyses will be conducted on an intention-to-treat basis using STATA statistical software release 12.0 (STATA, College Station, TX, USA). Per-protocol analysis will also be performed by including all participants who are at least 80% compliant in completing the exercise (as measured by the number of exercise sessions attended) and in taking the drinks and supplements (as measured from the compliance calendar and pill count). Baseline characteristics between the groups will be compared by independent *t* tests for continuous variables and chi-square tests for categorical variables. Wherever possible, we will obtain endpoint measures from all withdrawals and include all randomized subjects in our final data analysis. All data will be checked for normality prior to analysis, and skewed data will be log transformed prior to analysis. Time, group and group-by-time interactions will be examined using generalized linear mixed models with random effects. Potential covariates to be included in the model will include: age, sex, race or ethnicity, changes in medication and change in habitual physical activity or diet. Multiple regression analysis will be used to investigate whether changes in lean tissue mass, muscle size, density and strength and a reduction in metabolic or inflammatory markers are predictive of any exercise-induced improvements in glycaemic control and insulin sensitivity. All data will be presented as mean ± standard deviation or 95% confidence intervals. The significance level will be set at *P* <0.05 or smaller if adjustments are made for multiple comparisons.

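### Out-of-range glucose and insulin are dropped at every visit, so follow-up HOMA-2 values go missing because of their own size

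*Protocol article*

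**What the plan says.** The Primary outcome measures section of the protocol article makes HOMA-2 insulin resistance and β-cell function primary outcomes alongside HbA1c. Both are calculated from fasting glucose and insulin. The section then fixes a rule for the inputs: "extreme values of fasting plasma glucose ≤3 or ≥25 mmol/l or serum insulin <20 or >300 pmol/l will be excluded". The reason given is "as this is the validity range of the HOMA-2 calculation, based on specific insulin measures". The check behind the rule covers everything that is entered: "All data will be checked prior to importing into the calculator".

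The rule names no visit. The abstract and Table 1 place these measurements at three visits: "The primary outcome measures to be collected at baseline, 3 and 6 months". The rule therefore reaches two visits after randomisation.

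The Statistical analysis section says "The primary statistical analyses will be conducted on an intention-to-treat basis", and adds "Wherever possible, we will obtain endpoint measures from all withdrawals and include all randomized subjects in our final data analysis". The model is described as follows: "Time, group and group-by-time interactions will be examined using generalized linear mixed models with random effects". Skewed data are to be log transformed first.

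**The concern.** Fasting insulin above 300 pmol/l tends to mark the most insulin-resistant visits, and insulin below 20 pmol/l the least. Removing those visits after randomisation selects on the primary outcome. A likelihood-based mixed model is valid when missingness depends only on what was observed. Here it depends on the value that was removed, and a participant's other visits recover only part of that information.

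Identical cut-offs in the two arms do not give identical losses. The hypothesis is that the supplement improves insulin sensitivity, and the Background describes whey-protein as acting on insulin. If insulin falls in the intervention arm, that arm loses fewer high values and more low ones than control; if it rises, the pattern reverses. Either way, removing each arm's more extreme values tends to bring the two means together. At stake is the size of the treatment difference on two of the three primary measures, more than its precision.

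**Working it through.** **What can be checked against the plan.** The plan gives no expected share of out-of-range values, so there is no figure of its own to reproduce on this point. The nearest is the sample size for HOMA-2 insulin resistance (difference 0.7, SD 1.2, 90% power, two-sided 0.05). The usual formula is n per group = 2(1.960 + 1.282)² × 1.2² / 0.7² = 61.8, rounded up to 62, or 124 in total (126 with the t distribution). The plan states 140. That gap is on the safe side and does not bear on this point.

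**Power.** About 161 completers remain of 202 after 20% drop-out (202 × 0.8 = 161.6). Power for 0.7 with SD 1.2 is 95.9% with no values excluded, 94.0% with 10% excluded and 91.2% with 20% excluded. Loss of power is not the problem.

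**Share of follow-up values out of range (assumed inputs).** Take insulin as log-normal with median m and log-SD s, and a 20% reduction in the intervention arm (median 0.8m). Glucose limits are ignored.

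- Below 20: Φ((ln 20 − ln m)/s)
- Above 300: 1 − Φ((ln 300 − ln m)/s)

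Example with m = 100 and s = 0.6:

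- Control: z = −1.609/0.6 = −2.68 gives 0.4% below; z = 1.099/0.6 = 1.83 gives 3.4% above.
- Intervention (median 80): z = −1.386/0.6 = −2.31 gives 1.0% below; z = 1.322/0.6 = 2.20 gives 1.4% above.

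Control loses mainly high values. The intervention arm loses both tails more evenly.

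**Effect on the estimate.** This comes from a simulation of at least 1,000,000 participants per scenario, with a baseline to follow-up correlation of 0.7 on the log scale and HOMA-2 insulin resistance taken as proportional to insulin. The estimate is the between-arm difference in change from baseline. Exclusion applies at both visits. The true log difference is ln 0.8 = −0.223.

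| Median, log-SD | Follow-up values out of range, control / intervention | Log-scale shrinkage, excluded | Log-scale shrinkage, entered at limit | Raw-scale shrinkage, excluded | Raw-scale shrinkage, entered at limit |
|---|---|---|---|---|---|
| 70, 0.5 | 0.8% / 2.0% | 3% | 1% | 1% | 1% |
| 80, 0.6 | 2.4% / 3.1% | 5–6% | 3% | 7% | 4% |
| 100, 0.6 | 3.7% / 2.4% | 5% | 3% | 15% | 8% |
| 100, 0.7 | 6.9% / 5.3% | 9% | 6% | 24% | 16% |
| 120, 0.7 | 10.1% / 6.4% | 11% | 8% | 32% | 22% |

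A raw-scale example for 120, 0.7: the difference is −0.613 with all data, −0.417 with exclusion and −0.476 with limit entry. So 1 − 0.417/0.613 = 32% and 1 − 0.476/0.613 = 22%.

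**Two cross-checks.**

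- A separate grid with lower insulin (median 60 to 100 pmol/l, geometric SD 1.6 to 2.0) put 0.4% to 6.6% of control and 0.4% to 10.7% of intervention follow-up values out of range. Log-scale shrinkage was 1% to 11%.
- A likelihood fit to all three visits on the log scale, closer to the planned model, shrank the effect by about 8%, 8%, 12% and 16% in the last four rows of the table. The mixed model does not repair the loss.

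**The case against.** The rule has a stated technical reason: the calculator is not valid outside the range. It is fixed in advance, identical in both arms and applied to raw inputs before import, and assessors are blinded. Excluding insulin users and people with HbA1c above 10% should make very high glucose rare. All of this stands, and it rules out reading the rule as discretionary or data-driven deletion. But the validity range justifies not extrapolating with the calculator. It does not justify treating a real, measured extreme as no information.

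A reader might infer that the rule contradicts the intention-to-treat statement. The documents do not support that. The sentence on including all randomised participants is qualified and linked to follow-up of withdrawals. The rule drops values, not people: participants stay in their arm and their in-range visits still enter the model. It is a tension only.

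A reader might also take the raw-scale shrinkage of 15% to 32% as the size of the problem. The plan log transforms skewed data, and the scenarios that produce those figures assume skewed insulin, so the log-scale column is the relevant one. Nor should the 4% to 16% of participants who lose a value at either baseline or follow-up be quoted as post-randomisation loss. Baseline exclusions cannot be caused by treatment.

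Finally, tabulations and sensitivity analyses are commonly left to an analysis plan that is not shown, so their absence is no finding. The deletion rule itself is stated in the article.

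**Conclusion.** The point holds in a limited form. The article fixes a rule that removes post-randomisation HOMA-2 values according to their own components, and the planned model's assumption does not cover the resulting gaps. The likely direction is toward no effect. Under the assumed insulin distributions, about 1% to 10% of follow-up values are lost and the change-from-baseline effect shrinks by about 3% to 11% on the log scale. If the outcome were left untransformed, shrinkage would be about 1% to 32%.

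These sizes rest entirely on assumptions: log-normal insulin, a 20% reduction, a correlation of 0.7, HOMA-2 proportional to insulin, and no loss from the glucose limits. With a tight distribution the effect is small. HbA1c is untouched and power is barely affected. This is a modest weakness that is cheap to remove, not a threat to the trial as a whole.

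**What to change.** 1. Keep measured out-of-range follow-up values, either by entering them at the calculator's limit or by treating them as censored there. The wording must state the exact glucose limits used, because the present rule also excludes values of exactly 3 and 25 mmol/l.
2. Add a supporting analysis of log(fasting insulin × fasting glucose), which needs no range limit, on all participants with a sample.
3. Report out-of-range counts by arm, visit and tail. A total per arm can look balanced while the tails differ.
4. Reserve exclusion for documented sample or fasting errors, judged blind to arm.

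The cost is a few sentences and one extra model. The article says insulin will be assayed in a single batch at study completion and that recruitment is under way, so at that stage the rule can be changed before any trial insulin value exists.

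There are two limits. Entry at the limit removes only part of the shrinkage: about 1% to 8% remains on the log scale in these scenarios. And the insulin × glucose analysis supports HOMA-2 insulin resistance but not β-cell function.

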#### Secondary outcome measures

Secondary outcome measures will include changes in: body composition (lean tissue mass, muscle size and intramuscular fat), fat mass, muscle strength, blood pressure, blood lipids, adipokines and inflammatory markers, serum insulin-like growth factor-1 and 25(OH)D, renal function, diabetes medication (purpose, variety and dosage), health-related quality of life and cognitive function. Other covariates and variables of interest to be assessed include: anthropometry, habitual physical activity, diet and use of lipid-lowering and blood pressure medication. A summary of all the outcome measures is shown in Table 1.

##### Body composition

Total body and regional (arms and legs) lean tissue mass, fat mass and percentage body fat will be assessed using dual energy X-ray absorptiometry (Lunar Prodigy, GE Lunar Corp., Madison, WI, USA), using software version 12.30.008. A peripheral quantitative computed tomography scanner (XCT 3000, Stratec Medizintechnik GmbH, Pforzheim, Germany) will be used to measure muscle cross-sectional area, subcutaneous fat cross-sectional area and muscle density, as a surrogate measure of intermuscular adiposity, at the 25% femur site using methods previously reported [38]. Briefly, after performing a scout view of the distal end of the femur, scans will be taken at the 4% and 25% position of the femur. The slice thickness will be 2.3 mm, and the voxel size will be set at 0.3 mm at a scanning speed of 10 mm/s. Subcutaneous fat cross-sectional area will be determined by selecting the area with thresholds -40 to +40 mg/cm^3^ hydroxyapatite density (contour mode 3, peel mode 1), and the muscle cross-sectional area will be determined by subtracting the total bone cross-sectional area (threshold, 280 mg/cm^3^; contour mode 1, peel mode 2) and subcutaneous fat cross-sectional area from the total area of the distal femur (threshold, -40 mg/cm^3^, contour mode 3, peel mode 1). For consistency, all analysis of dual energy X-ray absorptiometry and peripheral quantitative computed tomography will be undertaken by a single investigator. The short-term coefficient of variation for repeated measurements of total body lean mass and fat mass in our laboratory ranges from 1.0% to 1.7%. The coefficient of variation for the femur muscle cross-sectional area is 1.3%.

##### Biochemical, hormonal and inflammatory markers

Following an overnight fast, participants will attend one commercial pathology clinic with multiple collection centres where rested, morning (8 to 10 am) venous blood samples will be collected. All blood will be sent to a central pathology laboratory accredited by the National Association of Testing Authorities Royal College of Pathologists Australasia. HbA_1c_ will be assessed by cation exchange HPLC using a Bio-Rad VARIANT II turbo HbA_1c_ kit-2.0 (Bio-Rad Laboratories, Hercules, CA, USA). Fasting plasma glucose will be assessed using the hexokinase method (Roche Diagnostics, Mannheim, Germany). Levels of C-peptide will be assessed using an electrochemiluminescence immunoassay and of high sensitivity C-reactive protein by an Immunoturbidimetric assay from Roche Diagnostics (Mannheim, Germany). Total cholesterol, high-density lipoprotein cholesterol and triglycerides will be determined using an enzymatic colorimetric method (Roche Diagnostics, Mannheim, Germany). Low-density lipoprotein cholesterol will be calculated using Friedewald’s formula. Serum creatinine, urea, albumin, calcium and phosphorus levels will be analyzed using standardized techniques. The estimated glomerular filtration rate (eGFR), as a measure of kidney function, will be calculated using the participants’ serum creatinine, age and sex according to the abbreviated ‘modification of diet in renal disease’ formula, which is now used by most laboratories in Australia:

eGFR (ml/(min 1.73 m^2^) = 175 × [serum creatinine (μmol/l) × 0.0113]^–1.154^ × age (years)^-0.203^] for men and eGFR (ml/(min 1.73 m^2^) = 175 × [serum creatinine (μmol/l) × 0.0113]^–1.154^ × age (years)^-0.203^ × 0.742 for women.

Serum aliquots will also be collected and stored at -80°C so that the following parameters can be assessed in a single batch at the completion of the study: levels of serum insulin, serum 25(OH)D, serum insulin-like growth factor 1, serum adiponectin and resistin, and a battery of pro-inflammatory and anti-inflammatory cytokines, including IL-6, IL-1β, IL-8, TNF-α and IL-10.

##### Blood pressure

After a 5-minute rest period seated in a quiet room, systolic and diastolic blood pressure will be measured using an automated blood pressure monitor (A&D Instruments, Oxon, UK). Four measurements will be taken on the left arm with a 2-minute interval between readings; the mean of the final three readings will be used in the analysis.

##### Muscle strength

Muscle strength of the lower limbs and upper back will be measured by employing a three-repetition maximum strength test for leg press and seated row exercises. This test determines the heaviest weight that can be used to complete three complete repetitions of an exercise whilst maintaining correct form and technique, and corresponds to ≈ 85% of an individual’s one-repetition maximum strength. Prior to the three-repetition maximum muscle strength test, participants will complete a 5-minute warm-up on an exercise bike. To determine the three-repetition maximum strength, each participant will initially perform a warm-up set of eight to ten repetitions with a light load. After successful completion of a further six to eight repetitions at a heavier weight selected by the instructing researcher and following a brief rest (≈2 to 3 minutes), the workload will be increased incrementally until only three repetitions with correct technique can be completed. For each participant, the formula employed by Wathen *et al.*[39] will be used to calculate each participant’s leg and back one-repetition maximum strength. In addition, isometric knee extensor strength will be measured on the participant’s dominant leg using Lord’s strap assembly, incorporating a strain gauge (Neuroscience Research Australia, Sydney, New South Wales, Australia). Participants will have one practice trial followed by two maximal tests with a 60 second rest between each test. This test has been shown to have excellent test-retest reliability (Pearson’s *r* = 0.92) [40]. For analysis, knee extension strength will be expressed per unit of lower leg length to compensate for the length of the lever arm.

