**Secondary outcome measures**				
Body composition	Dual energy X-ray absorptiometry total body and regional lean mass and fat mass, and bone density	×		×
	Peripheral quantitative computed tomography scan at 25% femur site	×		×
Biochemistry and hormonal measures	Routine biochemistry	×	×	×
	Serum 25-hydroxyvitamin D	×	×	×
Adipokines and inflammatory markers	Overnight fasted plasma collection	×	×	×
Blood lipids	Overnight fasted plasma collection	×	×	×
Blood pressure	Automated measurement	×	×	×
Muscle strength	Leg press and seated row	×		×
	Isometric knee extensor strength	×	×	×
Muscle function and balance	Timed up-and-go test	×	×	×
	Four-square step test	×	×	×
	30-second sit-to-stand test	×	×	×
Diabetes and other medication	Monthly reports	×	×	×
Health-related quality of life	Short Form (36) version 2 questionnaire	×	×	×
Cognitive function	CogState Brief Battery computerized tests	×	×	×

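### Knee extensor strength is to be divided by lower leg length to correct for the lever arm; for a strain-gauge force this enlarges the lever-arm effect (minor: no bias between arms)

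*Protocol article*

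**What the plan says.** Under Muscle strength, the protocol article states that "isometric knee extensor strength will be measured on the participant’s dominant leg using Lord’s strap assembly, incorporating a strain gauge". It then fixes the analysis variable: "knee extension strength will be expressed per unit of lower leg length to compensate for the length of the lever arm". The formula (division by length) and its purpose (correcting for the lever arm) stand in the same sentence. The article gives no unit for the reading and no strap position, and nowhere says that the reading is first converted to torque.

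Table 1 lists "Isometric knee extensor strength" as a secondary outcome at baseline, 3 and 6 months. Under Statistical analysis, multiple regression is to examine "whether changes in lean tissue mass, muscle size, density and strength and a reduction in metabolic or inflammatory markers are predictive" of improvement in glycaemic control and insulin sensitivity. On scale, the same section says that "skewed data will be log transformed prior to analysis"; otherwise the values are analysed as they stand.

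**The concern.** The muscle's output in an isometric knee extension is a torque about the knee. A strap gauge on the lower leg measures the force that balances this torque at some distance from the joint. The longer that distance, the smaller the force for the same torque. A lever-arm correction must therefore multiply the force by the distance. The rule as written divides, so it applies the lever-arm penalty a second time.

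Three things are at stake: whether the reported absolute values mean what the article says they mean, how much weight each participant's absolute change carries, and whether a strength-change predictor in the regression picks up stature. The primary outcomes are not touched.

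**Working it through.** **Inputs.** The rule, the device and the visits come from the article (Muscle strength; Table 1). The article gives no leg lengths, torques or gains, so every such value below is an assumption. The article states no figure on this point that could be reproduced.

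**Dependence on lever arm.** Moment balance gives T = F × L, so:
- raw force: F = T/L, which varies as 1/L
- planned value: F/L = T/L², which varies as 1/L²
- product: F × L = T, which does not depend on L

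**Two people with equal torque.** Take T = 100 Nm and L = 0.32 and 0.40 m.
- Raw force: 100/0.32 = 312.5 N and 100/0.40 = 250 N; ratio 1.25.
- Planned value: 312.5/0.32 = 977 N/m and 250/0.40 = 625 N/m; ratio 1.56, which is 1.25².
- Product: 100 and 100 Nm; ratio 1.00.

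The ratios do not depend on T. Over other assumed length pairs:

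| L (m) | Raw force ratio | Planned ratio | Product ratio |
|---|---|---|---|
| 0.38 and 0.42 | 1.105 | 1.222 | 1.00 |
| 0.35 and 0.45 | 1.286 | 1.653 | 1.00 |
| 0.32 and 0.48 | 1.500 | 2.250 | 1.00 |

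**If the reading is already a torque.** No lever-arm correction is needed, and T/L brings back a dependence on L. The stated reason fails on this reading too.

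**Change within a person.** With L fixed over 24 weeks, absolute change on the planned scale is (T₁ − T₀)/L², which is the true change times a personal constant. Percent change is (T₁ − T₀)/T₀, and log change is log T₁ − log T₀. L cancels from both.

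**How noisy is absolute change?** Simulation with L normal (mean 0.36 m, SD 0.03 m) and torque change independent of L:
- Mean change 0, SD 15 Nm: correlation with true change is 0.985 for the planned value and 0.996 for raw force.
- Mean change 15, SD 10 Nm: 0.954 and 0.988.

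**Link to stature.** In the same model the planned change is uncorrelated with L when mean change is zero. Its correlation with L is about −0.11 at mean 10, SD 15 Nm, and about −0.25 at mean 15, SD 10 Nm, although true torque change was generated independently of L.

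**The case against.** The strongest reply is that no planned between-arm conclusion is at risk. The outcome is secondary and is analysed as change and group-by-time. Leg length is effectively a fixed scale factor for each adult over 24 weeks. Randomisation balances it on average and is stratified by sex, and sex is a candidate covariate. If the data are skewed, the log transformation removes the factor from within-person change altogether. All of this stands.

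The 1.56 ratio is a comparison of absolute strength between people, which the article does not plan as an analysis. This also stands: the ratio shows the direction and form of the error, not the damage to a planned result.

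The regression text says only strength. It does not say that knee extension, rather than leg press or seated row, is the predictor, nor whether change is absolute or relative. The harm there is therefore conditional.

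A reader might also infer that the trial loses its only strength measure available at every visit. The article does not support this: it describes the 30-second sit-to-stand test as a measure of lower-extremity strength and function, and Table 1 schedules it at all three visits.

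Finally, no unit is given, and the phrase may be loose wording in a condensed article. Force is the natural reading of a strap strain gauge but remains a premise. The point survives, because the sentence gives both a formula and a purpose, and the formula does not serve that purpose whether the reading is force or torque. Division might be defended as body-size scaling, but that is not the reason given.

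**Conclusion.** The rule is wrong as written and the consequence is minor. On the natural reading that the gauge records force, dividing by lower leg length changes the dependence on lever arm from 1/L to 1/L² instead of removing it (1.25 becomes 1.56, not 1.00, at the assumed 0.32 and 0.40 m).

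A reader might infer that the treatment comparison for knee strength is biased. The documents do not support that, because length is constant within a person and balanced in expectation between arms. Nor do they support a firm statement that strength in taller people or men will be understated by a given amount, since that depends on how torque relates to stature, which the article does not give.

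The harm is limited to three things:
- absolute values that are mis-scaled and cannot be read as torque;
- some extra between-person noise in absolute change (correlation with true torque change about 0.95 to 0.99 under the assumed models);
- a modest association with stature (about −0.11 to −0.25 in the runs with non-zero mean gain) if absolute knee-strength change enters the regression.

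**What to change.** Replace the sentence under Muscle strength with one saying that knee extension strength will be expressed as torque (Nm): the recorded force multiplied by the lever arm. Use the lower leg length that the plan already relies on as the lever arm, or the knee-to-strap distance if it was recorded. Hold the value fixed for each participant across visits, and state the gauge's unit. Use torque in the outcome model and wherever knee strength enters the regression under Statistical analysis. If the device already reports torque, drop the division.

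The cost is one sentence and a recalculation. With lower leg length as the lever arm, no new measurement is needed. The knee-to-strap distance is not mentioned in the article and should be used only where it was recorded.
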